### Study design

This is a single centre, randomised two-arm feasibility trial, with a nested mixed-methods process evaluation.

### Setting

The study will be conducted in one maternity unit in inner city London, serving an ethnically diverse population and providing maternity care for over 6000 women annually.

### Target population

The target populations are women who are overweight (BMI 25–29.9 kg/m^2^) or obese (BMI ≥ 30 kg/m^2^) as identified at their first antenatal contact and women with a normal BMI (18.5–24.9 kg/m^2^) at pregnancy booking who gain excessive gestational weight as assessed at 36 weeks gestation [27]. Women will be eligible for recruitment if they meet the following criteria:
Aged 18 and overSpeak and read EnglishExpecting a single babyHave not accessed weight management groups during index pregnancy

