## Strengths and limitations of this study

Postnatal interventions may be more effective than antenatal interventions at supporting weight management among women with higher BMIs, but evidence is needed.This feasibility trial will assess if women with high BMIs at pregnancy commencement or have normal BMIs but gain excessive gestational weight would be prepared to be randomised to standard care plus Slimming World® (Alfreton, UK) groups offered from 8 to 16 weeks postnatally, or to standard care only.Women will only be recruited from one study site; however, the site provides maternity care to a population with wide diversity. The intervention is available UK-wide.Blinding of study participants and assessors is not possible.

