### Trial feasibility objectives

The trial feasibility objectives are as follows:
To assess recruitment and retention ratesTo estimate the effect size for a likely primary study outcome in a future definitive trial, namely difference between study groups in weight change from booking to 12 months postbirth, expressed as percentage of weight change or weight loss in kilogrammesTo estimate impact of lifestyle information and access to Slimming World® (Alfreton, UK) groups on maternal weight change from first antenatal visit to 12 months postnatallyTo explore influence of lifestyle information and access to Slimming World® (Alfreton, UK) groups including weight management, diet, physical activity, breastfeeding, smoking cessation, alcohol intake, physical and mental health, infant health, sleep patterns, body image, self-esteem, and health-related quality of life at 6 and 12 months postnatallyTo assess resource impacts across different agencies likely to be of relevance and identify data appropriate for economic evaluation in a definitive RCTTo decide if criteria to inform progression to a definitive RCT have been met

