### Recruitment

Women with BMIs ≥ 25 will be identified from their antenatal booking details. At approximately 26 weeks gestation, identified women in this group will receive a study letter which briefly explains study aims and advises that a research midwife will be in contact within 2 weeks to explain the study further. The letter will also explain how the woman can contact researchers if she does not want to receive further details. The research midwife will call women who have not asked to be removed from the contact list.

Women with normal BMIs at pregnancy commencement, but gain excess pregnancy weight as assessed at around 36 weeks gestation against IoM criteria [27], will be offered the opportunity to self-refer to the research midwives, through advertising at the study site and midwifery and obstetric referrals (from around 28 weeks gestation). Women will be asked to contact the research midwives to arrange to be weighed at around 36 weeks gestation. If women in this group do not respond to study advertising within 3 months of commencement of recruitment, a similar opt-out approach for women with high BMIs will be adopted, following relevant ethics amendments. An opt-out letter would be sent to all women with normal BMI at booking at around 32–34 weeks gestation to explore feasibility of this approach.

All women identified will be offered a patient information leaflet by research midwives prior to seeking consent at around 36 weeks gestation. Women interested in participating will be met by research midwives at the study site to obtain consent and complete the baseline questionnaire. Women who gain excessive gestational weight could be recruited at an antenatal appointment if this takes place around 36 weeks gestation.

All women who are eligible, recruited, and provide written consent will be randomised to either of the following:
Standard care plus lifestyle information and postnatal access to Slimming World® (Alfreton, UK) weight management groupsStandard care only

A screening form will be completed by the research midwife to record women approached, their eligibility, and at what point women may have declined to take part (when first approached or at consent) and reasons for this, if women are willing to provide information.

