### Trial feasibility objectives

The primary feasibility objective is to estimate the effect size for a likely primary study outcome in a future definitive trial, namely difference between study groups in weight change from booking to 12 months postbirth, expressed as percentage of weight change or weight loss in kilogrammes. Mean percentage change across all women gives greater power, and fewer women will need to be recruited. We will undertake pre-planned sub-group analysis of the primary assessment in women of different booking BMI categories. The primary endpoint for a future trial will be selected on grounds of power.

Other objectives include those most appropriate to support meeting the primary objective and inform progress to a definitive RCT. These will include rates of 5% and 10% weight reduction and changes in relation to aspects of healthy lifestyle and health behaviours, including diet and nutrition, breastfeeding, physical activity, smoking cessation, alcohol intake, self-esteem, and body image. Some included measures have been validated in relevant populations, including among women of reproductive age and women who have recently given birth.

Measures will be included in questionnaires at 6 and 12 months postnatally. Those marked with ‘**’ will also be included in the baseline questionnaire. Questionnaires will be ‘tailored’ for the intervention or standard care arm, to enable questions on uptake of support for weight management to be included at 6 and 12 months to inform trial process outcomes:
Dietary intake: The Dietary Instrument for Nutritional Education (DINE© University of Oxford)** [33]Soft drink intake: questions developed for the studyPhysical activity: The International Physical Activity Short-Form** [34]Mental health: Edinburgh Postnatal Depression Scale [35]Breastfeeding intent**, uptake, and duration, questions developed for studySleep patterns: questions developed for the studySmoking: smoking status/cigarette dependence** [36]Alcohol consumption: Alcohol Use Disorders Identification Test** [37]Self-esteem: Rosenberg Self-Esteem Scale** [38]Infant health: questions developed for studyImpact on body image [39]Resource utilisation and costs outcome measures: the EQ-5D-5L** and the Adult Service Use Schedule** [40]

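### Booking weight with no stated gestation limit sets eligibility BMI, BMI subgroup and starting weight, and the adjustment set omits gestation at booking

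*Protocol article*

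**What the plan says.** The Target population section defines two groups by the booking measurement: women overweight or obese "as identified at their first antenatal contact and women with a normal BMI" at booking who go on to gain excessively. The Recruitment section gives the source of the first group: "Women with BMIs ≥ 25 will be identified from their antenatal booking details".

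The proposed primary endpoint starts at the same measurement. Under Trial feasibility objectives it is the difference between groups in "weight change from booking to 12 months postbirth". That section also plans a subgroup analysis by booking BMI category and lists "rates of 5% and 10% weight reduction" among the other outcomes, without saying from which weight the reduction is counted.

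Other places describe the population by its BMI at the start of pregnancy. Strengths and limitations refers to "women with high BMIs at pregnancy commencement", Recruitment to "Women with normal BMIs at pregnancy commencement, but gain excess pregnancy weight as assessed at around 36 weeks gestation", and the Discussion also speaks of BMI at pregnancy commencement.

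The timings given are recruitment steps: "At approximately 26 weeks gestation, identified women in this group will receive a study letter", and consent follows at around 36 weeks. Neither limits how late the booking weight may be taken. The Analysis section lists the adjustment factors as parity, maternal age, ethnicity, booking BMI and, as appropriate, the baseline measurement. Gestation at booking is not listed.

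**The concern.** Booking BMI and BMI at pregnancy commencement agree only if booking is early. For a late booker the recorded weight is starting weight plus whatever she has gained so far, and that one weight feeds several parts of the plan:

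- **Eligibility.** A woman whose starting BMI is just under 25 can enter as overweight without having gained excessively. In the other direction, if gain to 36 weeks is counted from booking weight (the article does not say), a normal-BMI late booker's gain is understated and a true excessive gainer can be missed.
- **Subgroups.** The pre-planned BMI subgroup analysis, and the BMI interaction in the economic analysis, can hold women whose category does not reflect their starting BMI.
- **Endpoint.** Part of her change to 12 months is the end of pregnancy, not weight management. This happens in both arms. It adds variance, and it raises the absolute 5% and 10% rates if those are counted from booking.

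The variance matters here because the sample size section names the standard deviation as one of the parameters the trial must estimate. Booking BMI as a covariate cannot do the work of gestation, because it does not separate a woman who was overweight from the start from one whose booking weight includes gestational gain.

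**Working it through.** **Inputs from the article:** SD of percentage weight change 3.3; target difference 2 points; 90% power; 5% significance (taken as two-sided); 65 per group.

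**Assumptions, not in the article:** heights 1.55–1.75 m; gains before booking; weight retained at 12 months; share of late bookers p = 5–20%; upward shift of their starting weight d = 5–8 percentage points; an alternative SD of 6.5.

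**The plan's own figure.** n per arm = 2(1.960 + 1.282)² × 3.3² / 2² = 57.2, so 58. The stated 65 is not reproduced, but it is on the safe side and is a separate matter from this point.

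**Can it happen to an individual?** Take height 1.65 m and 65 kg at commencement, with 6 kg gained before booking and 2 kg retained at 12 months.
- BMI at commencement: 65 / 1.65² = 23.9. BMI at booking: 71 / 1.65² = 26.1, so overweight.
- Recorded change: (67 − 71) / 71 = −5.6%. Change from commencement: (67 − 65) / 65 = +3.1%.

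**How general is it?** Two conditions must both hold.
- To cross BMI 25 the gain must be at least (25 − BMI) × height².
- To show a 5% fall, the gain must be at least (w + r)/0.95 − w, where w is starting weight and r is retained weight. With r = 0 this is 1/0.95 − 1 = 5.26% of w.

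With nothing retained, over heights 1.55–1.75 m:
- starting BMI 23.75–24.9: a gain of 3.0–4.0 kg meets both
- starting BMI 23: 4.8–6.1 kg
- starting BMI 22: 7.2–9.2 kg

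At BMI 24 and 1.65 m (w = 65.3 kg), the gain needed for a 5% fall is 3.4 kg with nothing retained, 4.5 kg with 1 kg retained and 6.6 kg with 3 kg retained. A 3 kg gain with nothing retained gives booking BMI 25.1 but a fall of only 4.4%. The effect is real, but it is confined mainly to women who start close to BMI 25.

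**Effect on variance.** If a fraction p has its change shifted by d points, SD′ = √(SD² + p(1 − p)d²), and required n is multiplied by (SD′/SD)².

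| p | d | SD′ from 3.3 | n factor at 3.3 | n factor at 6.5 |
|---|---|---|---|---|
| 5% | 5 | 3.48 | 1.11 | 1.03 |
| 5% | 8 | 3.73 | 1.28 | 1.07 |
| 10% | 5 | 3.62 | 1.21 | 1.05 |
| 10% | 8 | 4.08 | 1.53 | 1.14 |
| 20% | 5 | 3.86 | 1.37 | 1.09 |
| 20% | 8 | 4.60 | 1.94 | 1.24 |

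For example, 3.3² + 0.05 × 0.95 × 5² = 10.89 + 1.19 = 12.08, and 12.08 / 10.89 = 1.11.

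**Effect on the arm difference.** Allocation is 1:1 by individual, so late bookers fall equally into both arms in expectation, and the expected difference is unchanged. Chance imbalance in late bookers is the same variance component already counted in SD′, not an additional harm.

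**The case against.** The strongest case against is that this is an argument from silence. The article condenses a longer protocol, which may set a window for the booking weight. The operative definition is also consistent: eligibility, subgroup and covariate all use booking BMI, and pregnancy commencement may be loose wording. On that reading a late booker sits in the subgroup exactly as defined. An SD that includes late bookers is also the right planning SD if the definitive trial uses the same baseline in the same population without further adjustment. Letters go out at about 26 weeks to women found from booking details, so that route mainly reaches women booked by then. Finally, the share of late bookers is wholly assumed.

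Most of this stands as a limit on size. It does not remove the point, because the article does state its adjustment set and that set lacks the one variable that would separate gestational gain from starting weight. The population description and the rule also differ within the Recruitment section itself.

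A reader might infer more: that any normal-weight late booker enters as overweight and then shows a 5% reduction, or that the trial's comparison is biased. The documents support neither. The first needs a starting BMI near 25, enough gain by booking and little retained weight. The second is ruled out in expectation by randomisation.

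**Conclusion.** The point holds as one of precision and interpretation, not of validity. The article sets no gestation limit on a weight that fixes eligibility BMI, BMI subgroup and the start of the proposed primary endpoint, and it does not adjust for gestation at that weight. The harm lies in outcome variance, in subgroups read as starting BMI, and in the absolute 5% and 10% rates. The last depends on those rates being counted from booking, which the article does not state.

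The size cannot be computed from the documents. The ranges of 1.1–1.9 (SD 3.3) and 1.03–1.24 (SD 6.5) rest entirely on the assumed shares and shifts. The upper end needs the most extreme of those together with the smaller SD, so the effect may well be small. If the full protocol already limits the gestation of the booking weight, one sentence in the article would settle the matter.

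**What to change.** Keep all women and the present eligibility rule. Then:

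1. Take gestation at the booking weight from the maternity record. It should be derivable there, although the article does not list it as a collected item.
2. Add it to the adjustment factors in the Analysis section.
3. Define late booking in advance, and report the weight-change, 5%/10% and BMI-subgroup results also without late bookers as a sensitivity analysis. Gestation at booking is fixed before randomisation, so this exclusion does not break the randomised comparison.
4. State the reference weight for the 5% and 10% rates.

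The cost is one extra covariate, one extra analysis and one clarifying sentence. No recruits are lost. The change does not repair eligibility: a woman classed as overweight because she booked late remains in the trial. An eligibility cut-off would address that but would cost recruits, and in a pragmatic feasibility trial it is not required.

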#### Exclusion criteria

Women will be excluded if they meet the following criteria:
< 18 years oldInsufficient understanding of spoken and written EnglishCurrent diagnosis of major psychiatric disorderFoetus has known abnormalityInvolvement in another postnatal study to reduce ‘burden’ of research participationIdentified medical complications (for example, cardiac disease, type 1 diabetes)Identified eating disordersPrevious surgery for weight management

### Recruitment

Women with BMIs ≥ 25 will be identified from their antenatal booking details. At approximately 26 weeks gestation, identified women in this group will receive a study letter which briefly explains study aims and advises that a research midwife will be in contact within 2 weeks to explain the study further. The letter will also explain how the woman can contact researchers if she does not want to receive further details. The research midwife will call women who have not asked to be removed from the contact list.

Women with normal BMIs at pregnancy commencement, but gain excess pregnancy weight as assessed at around 36 weeks gestation against IoM criteria [27], will be offered the opportunity to self-refer to the research midwives, through advertising at the study site and midwifery and obstetric referrals (from around 28 weeks gestation). Women will be asked to contact the research midwives to arrange to be weighed at around 36 weeks gestation. If women in this group do not respond to study advertising within 3 months of commencement of recruitment, a similar opt-out approach for women with high BMIs will be adopted, following relevant ethics amendments. An opt-out letter would be sent to all women with normal BMI at booking at around 32–34 weeks gestation to explore feasibility of this approach.

All women identified will be offered a patient information leaflet by research midwives prior to seeking consent at around 36 weeks gestation. Women interested in participating will be met by research midwives at the study site to obtain consent and complete the baseline questionnaire. Women who gain excessive gestational weight could be recruited at an antenatal appointment if this takes place around 36 weeks gestation.

All women who are eligible, recruited, and provide written consent will be randomised to either of the following:
Standard care plus lifestyle information and postnatal access to Slimming World® (Alfreton, UK) weight management groupsStandard care only

A screening form will be completed by the research midwife to record women approached, their eligibility, and at what point women may have declined to take part (when first approached or at consent) and reasons for this, if women are willing to provide information.

A separate patient information leaflet will be mailed to recruited women purposively selected from both trial groups and invited to participate in a telephone or face to face interview at 12 months postnatally. Similarly, women allocated to the intervention who are purposively selected for interview about their experiences on completion of their Slimming World® (Alfreton, UK) groups will be sent a separate study information leaflet to seek consent to participate in this stage of the study process evaluation.

### Treatment allocation and randomisation

Randomisation and allocation will be carried out by KCL’s Clinical Trials Unit web-based system. Women will be registered on the InferMed MACRO web-based data entry system by a research midwife prior to randomisation to allocate each a unique study number ‘PIN’. Research midwives will access the system and, using the PIN, initials, and date of birth, request randomisation. Unit of randomisation will be individual participant, allocated in a ratio of 1:1 to intervention and control. Selection bias will be minimised by ensuring all women eligible and recruited have equal opportunity of being allocated to each study group and follow-up completed, with information on women randomised and allocated but who opt out presented but clearly indicated as such. Use of intention to treat (ITT) analysis will limit attrition and analytical bias.

### Blinding

It will not be possible to ‘blind’ research midwives or women to allocation. Those responsible for analysis will be blinded to allocation.

### Interventions

Standard care (described below), plus information on positive lifestyle behaviours from late pregnancy and access to a 12-week weight management group (Slimming World® (Alfreton, UK)) commencing from 8 weeks up to 16 weeks postnatal (see Fig. 1 flow chart).

**Fig. 1 Fig1:**
[figure not shown]
CONSORT study flow diagram for supporting women with postnatal weight management (SWAN) feasibility trial

An evidence-based positive lifestyle leaflet reflecting current NICE guidance on breastfeeding, diet, importance of smoking cessation/prevention of relapse, reducing alcohol, and managing sleep [10, 28] will be offered to women allocated to the intervention.

Slimming World® (Alfreton, UK) content is underpinned by group behaviour change techniques targeted to support individuals make healthier food choices and increase physical activity (www.Slimmingworld.co.uk). Groups are run using a standardised approach, with in-built quality assessment procedures [7]. Behaviour change techniques are supported by social cognitive theory, with a focus on motivation and self-efficacy for weight management and reducing relapse, including goal setting, self-monitoring, social support, and positive reinforcement [29, 30].

Consultants who lead groups receive standardised training overseen by Slimming World® (Alfreton, UK) dietitians and nutritionists which includes motivational techniques to support positive lifestyle changes to manage weight, nutrition, food facts, and role of exercise and activity in health and weight management. Groups follow a standard format, starting with a weigh in, followed by discussion of group member’s experiences of weight management to help change habits, share healthy swaps, and discuss what to eat. Sessions can include basic cooking skills, taking cost, cultural preferences, and time constraints into account.

A food optimising system encourages adherence to healthy eating, and physical activity encouragement includes facilitation of behaviour change, redefining what ‘activity’ can include. Slimming World® (Alfreton, UK) will record initial and ongoing attendance and weekly weight. Women can attend for up to 12 groups at no-cost, which run over 14 consecutive weeks to allow 2 ‘holiday’ weeks within offer. After this time, women can choose to continue and pay the standard weekly fee.

A research midwife will contact women at 8 weeks postnatally to provide a dedicated Slimming World® (Alfreton, UK) telephone number for member services. A Slimming World® (Alfreton, UK) consultant will provide the woman with information on the local groups she can join, times, and venue (standard practice). Women can choose which group they attend and when they commence groups within the 8 to 16 week ‘window’ to fit with their health, lifestyle, and family demands. Women can take their babies with them.

We will assess adherence to allocation protocols, loss to follow-up, and women’s views of acceptability and sustainability. To capture data on whether women attend for each complete Slimming World® (Alfreton, UK) group session or leave after the initial weigh-in, we will ask women to complete in their follow-up questionnaires how many groups they attended and stayed for the whole session. Follow-up will capture data on women who continue attending groups or achieve their goal and stop attending to compare outcomes of interest with the control group.

Slimming World’s® (Alfreton, UK) quality assurance procedures ensure standardisation of weight management groups, including weekly calls between group consultants and their team managers. As consultants are from the local area, they will be aware of cultural preferences, time, and budget constraints women face and can advise on basic cooking skills and local shops selling healthy foods within women’s budgets. The Food Optimising system used in Slimming World® (Alfreton, UK) groups includes pictorial use of recipes for individuals who may not have a high level of understanding of written English. As our postnatal population is geographically mobile [31], women who move from the area can transfer their group membership to another local group anywhere in the UK.

Women from both trial groups will be asked to attend an appointment with a research midwife to be weighed either at the study site or at their home at 6 and 12 months. Travel costs and £10 Love2Shop voucher to thank women for their time will be offered.

